| Safety evaluation  Safety evaluation | For safety evaluation, the subjects are monitored for compliance including adverse events occurrence. The compliance is measured by controlling drug accountability during patients´site visits. From the time a patient consents to participate in the trial until he/she has completed the trial (without any follow up period), all AEs will be reported in the CRF. All SAEs as defined in the protocol will be reported by filling out and sending the SAE form within 24 hours to *the monitor*. *The sponsor* will determine whether the event qualifies to immediate reporting to the regulatory authorities (SUSAR-reporting) or will be reported in the annual development safety update report (DSUR). SAEs occurring after trial termination must be reported if considered related to the treatment during the trial. |
| Statistical methods | Non-parametric tests will be used. Mann-Whitney´s test; when comparison between groups. Statistical testing of multiple assessments over time; Kruskal-Wallis or Friedmans test and Wilcoxons test. |
| Criteria for evaluation | All subjects enrolled will constitute the analysis population  Primary and secondary endpoints (except safety parameters) will be analyzed according to intention to treat.  Safety parameters will be analyzed as per protocol. |
| Interim analysis | No interim analysis is planned |

- **Background and Rationale**
- **Background**

The two inflammatory diseases Rheumatoid Arthritis (RA) and Systemic Lupus Erythemato-sus (SLE) have the major comorbidity problem of Cardiovascular diseases (CVD) in common. The risk for CVD is overall more than doubled in both RA (1) and SLE compared with population/controls. In SLE, this risk for CVD is emphasized and noted 8 times increased in middle aged women (2, 3). In our further studies of surrogate markers and risk factors for CVD, we could show both an increased Intima-Media thickness and decreased endothelial function in RA compared with controls (4, 5). In SLE we have shown an increased vascular stiffness compared with controls (6). Traditional risk factors (e.g. dyslipidemia and hypertension) for CVD are increased in RA and SLE although with diverging results (7-10).

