To receive information in writing about the increased risk of CVD can worry the patient. However, we do have a strategy in answering the patients´ questions and also a structured plan for dealing with cardiovascular risk factors that need direct medical intervention. The patients will be able to reach the study nurse by phone at every site and if needed, the investigator is available for answers. If risk factors for CVD are in need of direct investigation or medical treatment, the patient will be remitted for this as in clinical praxis.

Taking part of the study will take a sufficient amount of time for the patient. However, the study is optional and contains a rigorous amount of tests regarding cardiovascular risk factors, which is of potential benefit for the patients.

Twenty patients in each group are needed for a 80%-ig power of lowering blood-pressure 10 mmHg. Lowering LDL or TC 0.65 mmol/L with SD 0.7 gives a power of 0.816 when 20 patients in each group are included.

- **Stop Criteria for the Study**

If any new alarming information regarding the safety profile of hydroxychloroquine in the studied population comes to the spnsoror´s knowledge during the trial, immediate actions will be taken to assess whether the study is to be stopped. See also section 17.5 “Study Closure”.

- **Study Visits**

Patients with RA and SLE will be recruited from the Rheumatology departments in Umeå, Sundsvall, Sunderbyn and Östersund. Our intention, if possible, is to recruit the same amount (n=24) of patients from each diagnoses. Patients full filling the classification criteria for RA (ICD-10 M05.9) and SLE (ICD-10 M32.9) and without ongoing HCQ-medication, will be invited to participate in the study. Information about the study, with informed consent and return envelope, will be sent by post, to the patients. The patient information will include name and phone number to nurse and physician from each center, for patients to ask any questions about the study. If the patient agrees to participate, a screening visit is booked with-in 2-3 weeks.

Two-three weeks before week 0 a **screening** visit is performed. After screening, randomization is performed.

Group 1 starts HCQ-medication at week 0. **Assessments** are performed at week 0, 4 and 8. After this the patients may continue the study medication outside the study due to the diagnose RA or SLE.

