Group 2 starts HCQ-medication at week 4. **Assessments** are performed at week 0, 4, 8 and 12. After this the patients may continue the study medication outside the study due to the diagnos RA or SLE.

See attachment 1. Schedule of events for more detailed description of the study procedures.

Each visit for assessments with blood samples and measurements of PWV takes 30 minutes + 30 min.

The medical treatment period within the study is 8 weeks for both groups. But the medication may continue due to the disease and diagnose.

**Screening:** Informed consent, inclusion and exclusion criteria are controlled (10.2). Disease activity is investigated regarding the diagnosis, **SLEDAI-2k** (attachment 3) for SLE and **DAS-28** (attachment 4) for RA. Medical history and present medication is recorded. Vital signs are investigated. For pre-menopausal women a pregnancy test is performed. Blood samples for analyses regarding disease activity is included in each diagnose-specific index (SLEDIA-2k and DAS 28). Analyses regarding blood lipids will also be performed (see also schedule of events). The screening visit takes 1.5 hour. After screening visit the patients are coded and randomly assigned to group 1 or group 2.

**SLEDAI-2k** is a disease activity index in SLE calculated from count of activity in all organs involved in this disease: Neuropsychiatric signs, visual disturbance, lupus headache, cerebrovascular incidence, vasculitis, arthritis, myositis, skin manifestations, serositis, signs of nephritis, hematological or serological manifestations and fever are recorded in this index (34).

**DAS-28** is a disease activity index in RA, used in every day-clinic. It is calculated from investigation of 28 joints, according to “swollen joints” and “tender joints”. Knees, shoulders, elbows, wrists, metacarpo-phalangial and proximal interphalangial joints are included in DAS-28. Patients global health, sedimentation rate, C-reactive protein-level and Health Assessment Questionnaire are also included in the calculation of DAS-28 (35).

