Patients with RA (n=24) and SLE (n=24) will be recruited from the Rheumatology depart-ments in Umeå, Sundsvall, Sunderbyn and Östersund. 12 patients with RA and 12 patients with SLE will be randomized to each group. The randomization will be performed by study nurses, not otherwise involved in the conduction of the study, so that patients with RA receive even study numbers (Group 1 or Group 2) and patients with SLE (Group 1 and Group 2) receive uneven study numbers. A randomization list definining each study numbers group identity/treatment regim is prepared in advance by the study team.

- **Eligibility Criteria**
- **Inclusion Criteria**
- Male and female, 18-65 years that have given their written consent to participate in the study; Women of Childbearing Capacity (WOCBC) only if willing to comply with effective contraception methods during the course of trial . Acceptable methods are such as oral contraceptives, contraceptive patches, contraceptive implant, vaginal contraceptive, double-barrier methods (for example, condom and spermicide), intrauterine device (IUD), hormonal IUD.
- ACR criteria for RA and SLE (4)
- < 10mg Prednisolon daily doses
- Low-medium disease activity = DAS28 <4.6-RA, SLEDAI <6 SLE (Arthritis accepted)
- **Exclusion Criteria**

A subject will not be eligible for inclusion in this study if any of the following criteria applies:

- Antimalarial medication less than 5 ½-t i.e. 250 days before inclusion visit
- High disease activity, where cortison adjustment is predictable
- Pleuritis or Pericarditis – SLE
- Impaired visus and/or color vision
- Auditory nerve damage
- Cardiomyopathy
- Brach block / atrioventricular block
- Hypertension >160/95
- Diabetes
- Ongoing medical treatment with digoxin
- Re-introduction or recent (within 2 weeks) change in the dosing of NSAIDs, prednisolon, blood pressure lowering medication or antilipide treatment and within 6 weeks for disease-modifying agents
- Serious comorbidity, including other medications with known drug interactions with medication intended in the present study
- Short life expectancy due to other comorbidity
- Documented allergy or intolerance to the study drug.
- Severe psychiatric condition or other reason that jeopardize compliance with visit schedule
- In case of women of child bearing capacity (WOCBC), pregnancy assessed by anamnesis and pregnancy test
- **Other Eligibility Criteria Considerations**

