Subjects who become pregnant during the trial must be withdrawn. The subject will be asked to attend follow-up visits and the outcome of the pregnancy will be followed including reporting on the state of the child 8 to 12 weeks after delivery. Patients receiving treatment shall not breast feed their children.

- **Data Analysis and Statistical Considerations**
- **Sample Size Considerations**

Twenty patients in each group are needed for a 80%-ig power of lowering blood-pressure 10 mmHg. Lowering LDL or TC 0.65 mmol/L with SD 0.7 gives a power of 0.816 when 20 pati-ents in each group are included.

- **Data Sets and Populations**

All subjects enrolled will constitute the analysis population.

- **Interim Analysis**

No interim analysis will be performed

- **Key Elements of Analysis Plan**

Non-parametric tests will be used. Mann-Whitney´s test; when comparison between groups. Statistical testing of multiple assessments over time; Kruskal-Wallis or Friedmans test and Wilcoxons test.

- **Study Administration**
- **Procedure for obtaining informed consent**

Eligible individuals in the study will be contacted by mail containing information about the study, informed consent and return envelope.

- **Definition of Source Data**

All completed assessment scales will be collected in patient specific binders and regarded as source data. All patient related activities of medical relevance will also be documented in the patient hospital record

- **Quality Control**

The trial will be monitored consistent with the demands of the trial and site activity to verify that the:

- Safety and rights of subjects are being protected
- Data are authentic, accurate, and complete
- Trial is conducted in accordance with the currently approved protocol and any other trial agreements, GCP and all applicable regulatory requirements. The investigator and the head of the medical institution (where applicable) agrees to allow *the monitor* direct access to all relevant documents.

An external monitor for the study, not involved in any aspect of the treatment of the individuals participating in the study, will be appointed. The monitor will be appropriately trained, and has the scientific and/or clinical knowledge needed to monitor the trial adequately.

The monitoring will take place in accordance to GCP before, during and after the trial. If any misconduct or neglect would be notified the sponsor and investigator will be notified for to corrective and preventive actions.

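### Kruskal-Wallis is listed for assessments over time, but it assumes independent samples and these are repeated visits of the same patients

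*Protocol*

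**What the plan says.** Section 16.1.3 (Key Elements of Analysis Plan) opens with "Non-parametric tests will be used". It then gives "Mann-Whitney´s test; when comparison between groups" and, for repeated visits, "Statistical testing of multiple assessments over time; Kruskal-Wallis or Friedmans test and Wilcoxons test". The Statistical methods row of the synopsis (section 4) carries the same list, ending in "Kruskal-Wallis or Friedmans test and Wilcoxons test". Neither place says when Kruskal-Wallis rather than Friedman would be used, which Wilcoxon test is meant, or whether Mann-Whitney is applied to follow-up values or to changes.

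Section 9 (Study Visits) sets the data structure. Group 1 assessments "are performed at week 0, 4 and 8"; group 2 assessments "are performed at week 0, 4, 8 and 12". "Group 2 starts HCQ-medication at week 4", so weeks 0 to 4 are the only period with an untreated concurrent group. Under section 10.1, "12 patients with RA and 12 patients with SLE will be randomized to each group", with separate number series for the two diagnoses, so diagnosis acts as a randomisation stratum. Section 16.1 bases the lipid sample size on 0.65 mmol/L, SD 0.7, 20 per group and power 0.816.

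**The concern.** Kruskal-Wallis compares independent groups of subjects. If visits are entered as groups, each patient appears in every group, and the stable differences between patients are counted as noise. The paired tests in the same sentence remove those differences. Friedman's presence after the word "or" does not cure this, because two tests that can give very different answers on the same data are both authorised without a rule for choosing. The trial is open label, and under section 19 the investigators run the analyses, so the choice should be closed in advance.

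The over-time tests also carry real weight. The primary objective asks for effects after 4 and 8 weeks of treatment. Because group 2 starts treatment at week 4, no untreated group exists at 8 weeks of treatment, and that part of the objective can only be answered within patients.

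**Working it through.** **1. Reproducing the protocol's own figure.** Inputs from section 16.1: difference 0.65 mmol/L, SD 0.7, 20 per group. The protocol states no alpha, so two-sided 0.05 is assumed. The standardised difference is 0.65 / 0.7 = 0.929. Two-sample t-test power (noncentral t) is 0.8163, which matches the stated 0.816. A paired t-test would give 0.976. The stated power therefore belongs to an unadjusted comparison of two independent groups. With the 24 per group actually randomised it is 0.883.

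**2. Kruskal-Wallis against Friedman: inputs.** 24 patients (one group, section 10.1) and three visits (group 1, section 9). SD 0.95 is the midpoint of the pilot's LDL SDs of 0.9 and 1.0 (section 5, pilot results). The fall of 0.4 mmol/L is the pilot's 3.4 minus 3.0, assumed to persist at the third visit. The within-patient correlation is not given in the protocol and is varied over 0.6, 0.7 and 0.8. Data are simulated as normal with a common correlation between visits, 3,000 trials per setting.

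**3. Results.**

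| Correlation | Kruskal-Wallis power | Friedman power |
| --- | --- | --- |
| 0.6 | 0.15 | 0.49 |
| 0.7 | 0.12 | 0.63 |
| 0.8 | 0.08 | 0.80 |

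With no true change, Kruskal-Wallis rejects in about 0.3% of trials or fewer, and Friedman in about 5%. Simulation error is about one percentage point on the powers.

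**4. Why it happens.** With correlation r between visits, differences between visit rank means have roughly (1 − r) times the variance they would have under independence, but the Kruskal-Wallis denominator does not shrink. For three visits its true type I error is therefore roughly 0.05 to the power 1/(1 − r). At r = 0.5 this is 0.05² = 0.0025, in line with a simulated 0.3% (SD 0.9). At r = 0.6 it is 0.05^2.5 = 0.0006. Simulated rates can run a little higher because the sample correlation varies with 24 patients.

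**5. Rough check on the correlation.** Read as a paired t-test on 7 or 8 patients, the pilot's p = 0.016 implies a correlation of about 0.93 to 0.95. Treating the two pilot visits as independent would give p of about 0.41 to 0.45. This is only indicative: an exact signed-rank test on 7 differences in one direction also gives 2 / 2⁷ = 0.0156. The conclusion does not depend on it.

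**6. Secondary point: group comparison at week 4.** Same inputs as step 1, t-based, 20 per group. SD of change = 0.7 × √(2(1 − r)); SD after baseline adjustment = 0.7 × √(1 − r²).

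| Correlation | SD of change | Power, change | SD adjusted | Power, adjusted |
| --- | --- | --- | --- | --- |
| 0.6 | 0.626 | 0.89 | 0.560 | 0.95 |
| 0.7 | 0.542 | 0.96 | 0.500 | 0.98 |
| 0.8 | 0.443 | 0.99 | 0.420 | 0.998 |

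Follow-up values alone give 0.816 throughout. Simulated Mann-Whitney power on follow-up values is 0.78 to 0.82. On change it is 0.65, 0.79, 0.96 and 0.99 at correlation 0.3, 0.5, 0.7 and 0.8, so change helps only above about 0.5. Adding diagnosis to the adjusted model moved power by about one point. With an assumed 0.5 mmol/L gap between diagnoses, Mann-Whitney on follow-up values had a type I error of about 3 to 5%.

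**The case against.** The strongest reply is that the defect is one alternative in a list. Friedman is offered in the same sentence, Wilcoxon follows it, and an analyst would probably choose correctly. Kruskal-Wallis also errs conservatively, so it cannot produce a false claim of benefit. Both statements are true and limit the damage, but neither makes the listed test suitable. It might also be said that Kruskal-Wallis was meant for comparing several independent subgroups; the sentence, however, assigns it to assessments over time.

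Some stronger readings are tempting but are not supported:

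- **That the stated tests as a whole do not fit the data.** Friedman does fit, and so does Wilcoxon if the signed-rank test is meant.
- **That the group comparison ignores baseline.** The response variable is unstated, and change from baseline is not excluded. This detail and the covariates may sit in a statistical analysis plan that is not shown. Mann-Whitney remains valid under allocation balanced by diagnosis.
- **That power between groups is only 0.56.** That figure joins the protocol's 0.65 difference to the pilot's SD of about 0.95. With the protocol's own SD of 0.7 it is 0.816.
- **That Friedman will drop many patients or mix untreated and treated weeks in group 2.** The protocol gives no missing-data rate and does not say that the test spans all four group 2 visits.

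**Conclusion.** Naming Kruskal-Wallis for repeated visits is wrong as written, in two places. Under the stated inputs its real type I error is about 0.3% or less against a nominal 5%, and its power is 0.15 to 0.08 where Friedman has 0.49 to 0.80. It would hide a real within-patient change of the size seen in the pilot. The direction of the error follows from the design; its size rests on the assumed correlation of 0.6 to 0.8, alpha 0.05, roughly normal data, and pilot values from a handful of SLE patients.

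The group comparison contains no error. Using the baseline already collected is a cheap gain: power 0.89 to 0.998 instead of 0.816 under the protocol's own inputs at the same assumed correlations. The diagnosis term adds little. Preferring ANCOVA or a mixed model to rank tests is a matter of choice.

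**What to change.** **Correction.** Delete Kruskal-Wallis from the synopsis and from section 16.1.3. Keep Friedman, and name the Wilcoxon signed-rank test for stated visit pairs; or use a linear mixed model with a patient effect and all available visits. In group 2, define the on-treatment comparison from the last untreated visit. That is week 4 under section 9. Section 11 gives week 5 as the start of treatment, so the two passages must be reconciled before this definition is written.

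**Optional improvement.** State that the week 0 to 4 group comparison uses change from baseline or baseline-adjusted values, with diagnosis as a factor or stratum: for example ANCOVA, or a van Elteren test on change. Week 0 serves as a common baseline, because Attachment 1 schedules no apolipoprotein sample at screening.

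**Cost.** Wording only, with no new data or visits. The parametric version needs a residual check, and skewed markers may need a log scale.

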ATTACHMENT 1. SCHEDULE OF EVENTS

| **Procedures** | **Screening**  **Week -2;** for eligible patients thereafter **Randomization** | **Week 0** | **Week 4** | **Week 8** | **Week 12 #** |
| --- | --- | --- | --- | --- | --- |
| Informed consent | X |  |  |  |  |
| Inclusion/Exclusion  Criteria | X |  |  |  |  |
| SLEDAI-2k (SLE) | X |  |  |  |  |
| DAS 28 (RA) | X |  |  |  |  |
| Medical history and present medication | X | X |  |  |  |
| Vital signs (pulse and blood pressure) | X |  |  |  |  |
| Pregnancy test* | X |  |  |  |  |
| Visus Color vision | X |  |  |  |  |
| Blood samples: |  |  |  |  |  |
| Chol | X | X | X | X | X |
| TG | X | X | X | X | X |
| HDL | X | X | X | X | X |
| LDL | X | X | X | X | X |
| ApoA1 |  | X | X | X | X |
| ApoB |  | X | X | X | X |
| Lp(a) |  | X | X | X | X |
| HbA1c | X | X | X | X | X |
| B-glc | X | X | X | X | X |
| CRP |  | X | X | X | X |
| Serum for storage  -20◦C. |  | X | X | X | X |
| PWV including  Pulse and blood  pressure |  | X | X | X | X |
| Adverse events |  |  | X | X | X |
| Compliance to drug prescription |  |  | X | X | X |

* For WOCBC

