To assess any potential impact on subject eligibility with regard to safety, the investigator must refer to the following documents for detailed information regarding warnings, precautions, contraindications, adverse events (AEs) and other significant data pertaining to study drug: Approved national summary of product characteristics (SPC).

- **Treatment within the study**

Hydroxychloroquine (Plaquenil®) 200 mg (Attachment 2. Summary of Product Characteristics) one tablet daily is initiated week 0 for group 1 and at week 5 for group 2and will be continued after the study is closed. All other medication continues during study, but if changes is performed in any medication, that might be a reason for discontinuation in the study (se also Section12.).

- **Withdrawal Criteria and Early Termination**

The subjects have the right to withdraw from the study at any time and for any reason without prejudice to his or her future medical care by the physician or hospital. The investigator also has the right to withdraw subjects from the study in the event of change in eligibility or other reasons.

Discontinuation criteria for individual subjects:

- Withdrawal of consent
- Changes in glucocorticoids, NSAID, ASA as well as medication against hyperlipidemia and hypertension
- Adverse event or serious adverse event related to treatment or investigational procedure that requires discontinuation in the study according to the investigator
- Pregnancy during the study
- **Study Assessments**
- **Demographic and Baseline Assessments**

Demographic information such as gender, age and ethnic origin will be collected in addition to baseline values.

Other baseline assessments are:

- Signed and dated ICF
- Inclusion/exclusion criteria
- Disease history/duration
- Current medication
- Disease activity by index (SLEDAI-2k or DAS 28)
- Vital signs
- WOCBC, pregnancy test
- Visus and color vision
- Blood lipids and-glucos
- See also Schedule of events, Attachment 1.
- **Assessments during the study**

Assessments include blood lipids, vascular stiffness, Calprotectin and Hyaluronan as described in 7.1 and 7.2 and 9.1.
In addition;

- Compliance to treatment
- Adverse events
- Compliance to drug prescription
- **Biobank**

Biobank is available at the Rheumatology Clinic, NUS, Umeå, Sweden (SoS443)

- **Study medication and concomitant medication/therapy**
- **Study medication per treatment group**

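### Group 2's only pregnancy test is 6-7 weeks old at its first hydroxychloroquine dose, with no test or eligibility re-check after screening and no medical history after week 0

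*Protocol*

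**What the plan says.** Attachment 1 marks the pregnancy test at screening and at no later visit: "Pregnancy test* | X", with a footnote limiting it to women of childbearing capacity. The inclusion and exclusion check is likewise marked at screening only. Medical history and medication appear twice, at screening and week 0, for both groups: "Medical history and present medication | X | X". The week 4 column holds blood samples, pulse wave velocity with pulse and blood pressure, adverse events and drug compliance.

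The visit text in section 9 agrees. Screening takes place "Two-three weeks before week 0", and the test is described under that visit alone: "For pre-menopausal women a pregnancy test is performed". Group 1 begins treatment at week 0. For the other arm, "Group 2 starts HCQ-medication at week 4".

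Section 10.2.2 excludes pregnancy on the basis of both history and a test. Section 10.2.1 admits women of childbearing capacity "only if willing to comply with effective contraception methods during the course of trial". Section 12 lists "Pregnancy during the study" among the reasons to discontinue, and section 15.4 requires withdrawal and follow-up of the pregnancy.

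**The concern.** The protocol requires a test as well as a history to exclude pregnancy, so it does not treat a woman's own account as sufficient. In group 1 that standard is applied fairly close to exposure. In group 2 the delayed start adds four weeks between the test and the first tablet, and the schedule does not repeat the test at the visit where treatment begins. A pregnancy that starts after screening could go unrecognised until after the first dose, although the protocol would have barred that woman from treatment.

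This is a participant-safety matter. It does not touch the analysis set or any efficacy comparison.

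**Working it through.** The plan states no age for the test, so there is no figure to reproduce. The check is date arithmetic followed by a rough yield estimate.

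**Age of the test at first dose** = (screening to week 0) + (week 0 to first dose). Inputs are from section 9; the Attachment 1 header gives screening as week -2, the lower end of the same range.

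| | Screening to week 0 | Week 0 to first dose | Age of test |
|---|---|---|---|
| Group 1 | 2-3 weeks | 0 | 2-3 weeks |
| Group 2 | 2-3 weeks | 4 weeks | 6-7 weeks |

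**What is scheduled between screening and group 2's first dose.** At week 0: medical history and medication, but no test or eligibility check. At week 4: adverse events and compliance, but no test, medical history or eligibility check.

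**Expected conceptions between test and first dose** = women x annual contraceptive failure rate x weeks / 52. Section 10.1 gives the group size: "12 patients with RA and 12 patients with SLE will be randomized to each group", so 24 per group. The other inputs are assumptions, not in the protocol: 6-18 of the 24 are women of childbearing capacity, and contraception fails in 1-9% per year.

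- Group 2, low: 6 x 0.01 x 6/52 = 0.007. High: 18 x 0.09 x 7/52 = 0.22.
- Group 1, low: 6 x 0.01 x 2/52 = 0.002. High: 18 x 0.09 x 3/52 = 0.09.

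These count all conceptions after screening, including those the woman would notice herself.

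**Share a test at first dose would detect** = (weeks - lag) / weeks, where the lag from conception to a positive test is assumed to be 2 weeks, varied from 1 to 3.

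- Group 2, lag 2: 4/6 = 67% to 5/7 = 71%. Lag 1: 5/6 = 83% to 6/7 = 86%. Lag 3: 3/6 = 50% to 4/7 = 57%.
- Group 1 at week 0, lag 2: 0/2 = 0% to 1/3 = 33%.

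**Expected pregnancies found by a week 4 test in group 2**, lag 2: 6 x 0.01 x 4/52 = 0.005 to 18 x 0.09 x 5/52 = 0.16.

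Conceptions just before screening, too early for the screening test to show, are left out. Trial contraception did not yet apply to them, and the protocol gives no basis for a rate.

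**The case against.** The strongest reply is that safeguards exist and the yield is tiny. Contraception is mandatory, adverse events are asked about at week 4 before group 2's first tablet, the investigator may withdraw anyone whose eligibility changes, and pregnancies are followed after delivery. That is fair, and it lowers the risk. None of these steps is a test, however; each relies on effective contraception or on the woman knowing and saying that she is pregnant.

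Second, the upper assumption may be generous. The pilot study in the Background section had nine SLE patients with a median age of 54 (44-64). The trial admits ages 18-65 and also RA, so the pilot does not settle the number, but 18 of 24 may well be high. This pulls the estimate towards its lower end.

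Third, harm is not demonstrated. The product information is not among the pages at hand, and section 8.2 describes the drug as long approved with a well-documented safety profile. No claim of material fetal risk from a brief exposure can be made here.

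Fourth, neither group is tested during its 8 weeks on treatment, so a week 4 test closes only part of the untested time. That is true. The point is limited to applying the protocol's own entry exclusion at first exposure.

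Two stronger readings are tempting and should not be adopted. A reader might infer from section 11, which says week 5 for group 2, that the test is older still. The synopsis counts treatment as weeks 1 to 8 and weeks 5 to 12, so its fifth week begins at time point week 4. A literal week 5 start plus 8 weeks would end at week 13, past the last visit and the 12-week study period. A reader might also infer that group 2 has no history at all between screening and first dose; Attachment 1 marks one at week 0 for both groups.

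**Conclusion.** The gap is real and modest. The intervals of 6-7 weeks for group 2 and 2-3 weeks for group 1 follow from the protocol's own timings and need no assumption. After screening, group 2 has no scheduled test or eligibility re-check, and after week 0 no medical history, before its first dose at week 4. The protocol does not contradict itself; its pregnancy exclusion is simply not re-applied when group 2 is first exposed.

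The expected yield of a repeat test is well below one pregnancy in the whole trial. That estimate rests on assumed numbers of women of childbearing capacity, contraceptive failure rates and detection lag. Almost all the gain lies in group 2, because a week 0 test in group 1 would come too early to show most conceptions since screening. This is a cheap improvement of minor priority, not a defect that should hold up the trial.

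**What to change.** In Attachment 1, add a pregnancy test at week 4 for women of childbearing capacity in group 2, to be done before the first tablet. In section 9, add one sentence: hydroxychloroquine starts in group 2 only after that test is negative. With this change the test is 0 weeks old at group 2's first dose.

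The cost is one schedule entry, one sentence, and one simple test per eligible woman at a visit that already takes place and already includes blood sampling. The downside is a rare withdrawal before dosing, which the protocol would require anyway once the pregnancy was known. A week 0 test in group 1 is optional and would add little.
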